#### Secondary Outcomes

Secondary outcome measures will include minutes of moderate PA per day, PA questionnaire, body mass index, blood pressure, physical performance, social support for physical activity, self-efficacy in a PA setting, behavior problems, and goal attainment. See Table 1 for a summary of all outcome measures.

**Table 1 table1:** Summary of outcome measures.

Measurement	Type of outcome	Measure
Steps per day	Primary outcome	Fitness tracker
Minutes of moderate activity	Secondary outcome	Fitness tracker
Body mass index	Secondary outcome	kg/m^2^
Blood pressure	Secondary outcome	Blood pressure monitor
Physical performance	Secondary outcome	Short Physical Performance Battery [50]
Behavior problems	Secondary outcome	Aberrant Behavior Checklist–Community [51]
Social support for PA and self-efficacy in PA setting	Secondary outcome	The Self-Efficacy/Social Support for Activity for Persons With Intellectual Disability scale [35]
Goal attainment	Method, secondary outcome	Goal attainment scaling [39]
Satisfaction with life	Control for adverse effects	Satisfaction with life scale [52]

##### Physical Activity

The secondary PA outcome is the number of minutes of moderate PA per day, measured with the commercial accelerometer.

In addition, the International Physical Activity Questionnaire-Short Form, adapted to measure PA using proxy respondents, will be used [53]. The International Physical Activity Questionnaire-Short Form is a 7-item questionnaire that assesses PA in the past 7 days at 4 intensity levels: (1) vigorous-intensity activity, such as aerobics, (2) moderate-intensity activity, such as leisure cycling, (3) walking, and (4) sitting.

##### Body Mass Index and Blood Pressure

Body mass index will be calculated in kg/m^2^ [54]. Blood pressure will be measured using a blood pressure monitor (Welch Allyn Inc). Height will be measured in meters with a stadiometer (Seca GmbH), with the participant wearing no shoes. Weight will be measured in kilograms with an analog floor scale (Seca GmbH), with participants wearing no shoes or outdoor jackets/gear. Waist circumference will be measured 1 cm above the navel.

##### Physical Performance

The Short Physical Performance Battery (SPPB) will be used to assess physical performance. The SPPB is a screening test designed to evaluate physical performance and predict disability in older adult populations [50]. The SPPB is mainly a measure of lower-extremity function and consists of 3 subtests: static balance, gait speed, and lower limb strength. To measure static balance, the participant is asked to stand with feet in the side-by-side, semitandem, and tandem positions, for 10 seconds each, to his or her best ability. Gait speed is measured with a 4-m (13-ft) walk at the individual´s habitual pace. Lower limb strength is measured by having the participant rise from a chair with arms folded across his or her chest, to his or her best ability. Subtest scores range from 0 (inability perform the test) to 4 (highest level of performance). The SPPB has been validated [55], and reference values have been published [56]. The Norwegian version of the SPPB appears to have acceptable reliability as well as good internal consistency in an older population with and without dementia [57]. The SPPB has been used in people with mild and moderate IDs [58,59].

##### Behavior Problems

The Aberrant Behavior Checklist—Community (ABC-C) is a questionnaire designed to assess challenging behavior in children, youth, and adults with IDs [51]. The checklist consists of 58 items divided into 5 subscales: irritability, lethargy, stereotypy, hyperactivity, and inappropriate speech. It is a proxy measure requiring knowledge of the person with ID. Each item is scored on a scale of 0 to 3 (3 indicating the highest severity). The ABC-C is a widely used behavioral rating scale used among people with IDs. A Norwegian study [60] examined the construct validity of the Norwegian ABC in a clinical sample of children and youths in Norway and found satisfactory psychometric properties for the ABC, with the exception of the inappropriate speech factor. The Cronbach coefficients were adequate to excellent, with coefficients ranging from .76 to .95. The ABC subscales were moderately to highly correlated with one another (*r*=0.41-0.78, *P*<.001).

##### Social Support for Physical Activity and Self-Efficacy in a PA Setting

The Self-Efficacy/Social Support for Activity for Persons with Intellectual Disability scale [35] is a questionnaire consisting of 4 subscales. One subscale measures self-efficacy for overcoming barriers to leisure PA. The last 3 subscales measure social support for leisure activity from family members, care staff, and friends for individuals with IDs. The scale has been validated for self-reporting from individuals with mild to moderate IDs and for use by proxy respondents [35]. The questionnaire will be translated into the Norwegian language using standard guidelines [61].

##### Goal Attainment

Goal attainment scaling [39,62] will be used to identify self-management goals that participants would like to achieve. The questionnaire will be filled out by the researcher, with participants and proxy respondents present. Goal attainment scaling involves several steps. Goals are selected by each individual, and observable behavior that reflects a degree of goal attainment is defined [63]. The participant’s pretreatment or baseline levels are defined in terms of the goal. Five different goal attainment levels are used, ranging from “no change” to “much better than expected outcome” (numbered –2 to +2). Follow-up times for participant evaluation are set after 3 months and 6 months. Goal attainment is evaluated after the defined time interval. At the end, the overall attainment score for all goals are calculated. In this study we will define up to 3 goals for PA [64]. The scale has been validated for use in rehabilitations populations [39] and has been used in studies with individuals with IDs [40,65].

##### Satisfaction With Life

This study will use the satisfaction with life scale developed by Bergström and Hochwälder [52], which was designed to assess satisfaction with the home environment and leisure time in individuals with mild to moderate IDs. The scale has 4 factors: (1) satisfaction with housing environment, (2) satisfaction with life, (3) satisfaction with meals, and (4) satisfaction with recreational activities. Items are read aloud by a researcher and answered by participants with 3 response options: good (happy face=2), in between (neutral face=1), or bad (sad face=0). In the current study, the scale is used to control for adverse effects.

#### Data Integrity

Patient- or proxy-reported and assessor-reported data are partly captured electronically using Research Electronic Data Capture (REDCap) (Vanderbilt University). REDCap is a web-based system that is compliant with relevant regulations and security requirements. The system has an integrated function for randomization. Questionnaires can be sent electronically to participants or the proxy respondent. Data not captured electronically, such as background information and physical performance test results, are registered at the baseline meeting. The study coordinator will evaluate the data of all participants for completeness. In cases of missing data, respondents will be contacted.

### Statistical Analyses

#### Sample Size

The study will be powered based on the primary outcome of accelerometer-measured steps per day (mean of 4 days) [4,66]. With a 2-group design and effect size of 0.8, power of 80%, and of .05, the expected minimum total sample size is 50 participants (25 participants in each group). The effect size in the current study is estimated based on previous studies, which have reported Cohen *d* values ranging from 0.29 to 0.91 [14,37,67]. An effect size of 0.8 is considered to be a clinically relevant difference between the 2 groups, corresponding to an increase in steps per day of approximately 2000 in the intervention group, which is also expected to be achievable [14]. To avoid underpowering the study and to prepare for expected dropout, we will recruit 30 participants per group, for a total sample size of 60 (Figure 3). The group size estimated is supported by other randomized controlled study protocols [27,37] and published results [68] of studies to enhance levels of physical activity in individuals with ID.

#### Data Analyses

The randomized controlled trial includes repeated measures in 2 groups, and linear mixed models will be used in the efficacy analyses of the intervention. In addition to a group variable (treatment or control), follow-up time (3 months and 6 months) and mean steps (with baseline comparison) will be added as covariates. An intention-to-treat approach will be used with a significance level of *P*<.05 and a secondary per-protocol analysis. All analyses will be performed using SPSS 26 software (IBM Corp).

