### Randomization

Participants will be randomized with a computer program to either the PA intervention with mHealth support group or the standard care control group.

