### Data Collection

Data will be collected at baseline, 3 months, and 6 months, as seen in Figure 3. Baseline data will include baseline PA activity level and will be collected before randomization. Follow-up data will be collected regardless of the participant’s compliance with the study protocol. Participants and assessors will not be blinded. Background data on the participants will be collected at baseline and will include age, gender, educational level, marital status, living condition, employment status, educational status, job-related or day center activities, leisure time activities, smoking habits, level of ID (ie, mild, moderate, severe, or profound), genetic diagnosis, gross motor function classification [42,43], communication level [44], medical history/readiness for the PA intervention, and use of medication. In addition, we will ask questions about barriers for participation in physical activities.

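### The stated steps model leaves out level of intellectual disability, a recorded baseline factor that could be added as one two-class covariate at little cost

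*Protocol article*

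**What the plan says.** Under Inclusion and Exclusion Criteria, the protocol article admits all four levels of ID and people who walk with or without support. Entry is limited to those with a sedentary lifestyle or low physical activity.

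Under Data Collection, the background data recorded at baseline include "level of ID (ie, mild, moderate, severe, or profound), genetic diagnosis, gross motor function classification". Baseline data are collected before randomisation.

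Under Data Analyses, efficacy is assessed with linear mixed models. Besides the group variable, "follow-up time (3 months and 6 months) and mean steps (with baseline comparison) will be added as covariates". This is a positive list, and it contains neither level of ID nor gross motor function.

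Under Sample Size, the calculation is an unadjusted comparison: "With a 2-group design and effect size of 0.8, power of 80%, and of .05" leads to the statement that "the expected minimum total sample size is 50 participants (25 participants in each group". To allow for dropout, "we will recruit 30 participants per group, for a total sample size of 60".

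**The concern.** Sixty people ranging from mild to profound ID are a very mixed group. Two participants with the same baseline step count but different levels of ID may well differ in later steps. The intervention works through an app, tailored communication and a support person, and the Discussion asks whether such support can be adjusted to different levels of functioning. The authors thus treat level of functioning as relevant to response, yet the stated model does not use it.

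Two things are at stake. First, any variance that ID level explains beyond baseline steps stays in the error term, and a chance imbalance in ID level is corrected only as far as baseline steps carry it. Second, a mixed model relies on data being missing at random given what is in the model. Sample Size allows for expected dropout, and the outcome needs at least 3 consecutive days of watch wear. If ID level affects both wear and steps, leaving it out weakens that assumption. The link to wear is plausible, but the documents do not state it.

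**Working it through.** **The plan's own figure.** Inputs from Sample Size: effect size 0.8 and power 80%. The significance level is 0.05; two-sided is assumed because it reproduces the stated number. Per arm: 2 × (1.960 + 0.842)² / 0.8² = 24.5, rounded up to 25, so 50 in total. This matches, and it takes no credit for any covariate. The sample size is therefore not in question.

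**Scale.** The article equates the effect size of 0.8 with about 2000 steps, so the implied SD is 2000 / 0.8 = 2500 steps. The correlation between baseline and follow-up steps is not given. Assuming 0.6, the SD left after baseline adjustment is 2500 × √(1 − 0.36) = 2000 steps.

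**Precision from one two-class ID term.** Let q be the proportion with severe or profound ID, and b the difference in later steps between the two classes at equal baseline steps. Neither is in the documents; q = 0.25 to 0.40 and b = 500 to 1500 are assumed. The share of residual variance removed is q(1 − q)b² / 2000². With 60 participants, k extra terms inflate the expected variance by 56 / (56 − k) relative to the model with group and baseline steps, so the equivalent sample size is 60 / (1 − share) × (56 − k) / 56. This treats one follow-up visit as an approximation to the mixed model.

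| q | b (steps) | Share removed | Equivalent n before cost | After cost, 1 term |
|---|---|---|---|---|
| 0.25 | 500 | 1.2% | 60.7 | 59.6 |
| 0.25 | 1000 | 4.7% | 63.0 | 61.8 |
| 0.40 | 1500 | 13.5% | 69.4 | 68.1 |

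One term breaks even at a share of 1/56 = 1.8%. That corresponds to b of about 617 steps at q = 0.25 and 546 steps at q = 0.40, from b = 2000 × √(0.0179 / [q(1 − q)]).

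**A second term.** If a two-class motor term explained nothing further, the same rows would give 58.5, 60.7 and 66.9.

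**Worst-case cost.** If the added factors are unrelated to later steps, the standard error grows by √(56/55) = 1.009 for one term and √(56/54) = 1.018 for two. With 50 participants the factors are √(46/45) = 1.011 and √(46/44) = 1.022. Five extra terms at 50 participants would cost about 6% and would have to explain roughly 10% of the residual variance to pay for themselves.

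**Chance imbalance.** Suppose allocation were simple, with 30 per arm. If 15 of 60 have severe or profound ID, a split of 10 v 5 or worse has hypergeometric probability 0.233. With b = 1000, a 10 v 5 split shifts the adjusted estimate by 5/30 × 1000 = 167 steps. If 24 of 60 do, a difference of 6 or more has probability 0.187, and a difference of 6 shifts it by 6/30 × 1000 = 200 steps. The standard error on the same inputs is 2000 × √(2/30) = 516 steps, so the shifts are 0.32 and 0.39 of a standard error.

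**Power.** With 50 participants, effect size 0.8 and correlation 0.5, baseline adjustment alone gives 89%. Two added terms give 87% if they explain none of the residual variance and 93% if they explain 20%. With effect size 0.5 and correlation 0.6, the figures are 57% for baseline only and 55% to 65% with two terms.

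**The case against.** The strongest reply is that a randomised comparison adjusted for the baseline value of the outcome is a valid, standard primary analysis, and that further covariates are optional. That stands: the plan contains no error here, and the point is an improvement.

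A reader might go further and infer that imbalance in ID level is left uncorrected, or that the result would be biased. The documents do not support this. Whatever ID level does to habitual steps is already carried by baseline steps; only its effect at equal baseline remains. Chance imbalance under randomisation neither biases the estimator nor inflates the type I error, and shifts of 167 to 200 steps are well inside the standard error.

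A reader might also conclude that the trial definitely gives up precision. That cannot be stated as fact. Every input to the gain is assumed, and in the weakest scenario the term costs slightly more than it returns. Limiting entry to sedentary or low-active people may also narrow the spread of the outcome.

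Finally, a reader might infer that allocation is unstratified, because Randomization says only that "Participants will be randomized with a computer program to either the PA intervention with mHealth support group" or the control group and names no factor. The article does not say so. It condenses a fuller protocol, which could name a stratification factor, so its silence is not a finding.

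What remains is the model. There the article is not silent: it lists the covariates, and level of ID is not among them.

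**Conclusion.** The point holds as a low-cost improvement to the stated model. A recorded, plausibly prognostic factor is absent from the covariate list. A single two-class ID term changes the equivalent sample size from 60 to somewhere between 59.6 (about nil) and 68.1 (a modest gain). That range rests on a residual SD of 2000 steps, 25-40% severe or profound ID, and 500-1500 steps between classes at equal baseline, none of which the documents give. The term also makes the missing-at-random assumption more credible; this benefit is not quantified here.

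The case for gross motor function is weaker. No benefit has been quantified for it, and several motor-class terms could cost more precision than they return.

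All this reads the phrase about mean steps as adjustment for baseline steps. The wording is loose; if baseline steps were not in fact a covariate, the gap would be larger.

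**What to change.** In Data Analyses, prespecify level of ID in two classes (mild/moderate v severe/profound) as a baseline covariate in the steps model. Add gross motor function only as a single two-class term, if at all. If the full protocol stratifies randomisation by any factor, include that factor in the model too.

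The cost is one sentence and one or two degrees of freedom, with the 1-2% larger standard error shown above as the downside. No new data are needed. According to Results, enrolment had not started, so the change can be made before any outcome is seen. That matters because assessors are not blinded, and a covariate chosen later could be challenged as post hoc.

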## Results

The project is approved by the Regional Committee for Medical and Health Research Ethics in northern Norway and is registered at ClinicalTrials.gov. Enrollment was planned to start in April 2020 but will be delayed due to the pandemic situation. Participant recruitment for the randomized controlled study will be initiated as soon as practical difficulties due to the pandemic situation are solved. Participants will be recruited, randomized, and administered the intervention individually. The main contribution of this paper is a detailed plan to run our study, which will produce new knowledge about mHealth to support PA in individuals with IDs.

## Discussion

The present trial will investigate how modern technology and mHealth can be used in the promotion of PA in individuals with IDs. A tailored PA program is expected to increase levels of PA, and individuals with IDs and low PA have the greatest chances of improving [13]. Throughout our project, we have used an ecological approach, and we are currently developing a theory-based mHealth motivational support system for the promotion of PA, which we believe will increase the probability of improved levels of PA. Focusing on the communication abilities of each participant and individual goal setting may be particularly important [64]. As previous research has shown difficulties in recruitment and data collection, including missing follow-up data [13], we will be prepared to meet these challenges.

By including individuals with all types of IDs and low levels of PA, we can add to the knowledge on whether mHealth support can be successfully adjusted to individuals with different levels of functioning and whether it can increase levels of PA [5]. There is evidence demonstrating that an mHealth intervention for PA can improve self-efficacy in activities, social support [32], health conditions such as blood pressure [13], and the results of physical performance tests [69]. This study has potentially important implications for both individuals with IDs and their support networks. If successful, the project will provide a simple and accessible solution for promoting PA in individuals with IDs. For widespread clinical implementation, it is necessary to engage stakeholders who support individuals with IDs throughout their lives.

## Abbreviations

ABC: Aberrant Behavior Checklist
ABC-C: Aberrant Behavior Checklist—Community
ID: intellectual disability
mHealth: mobile health
PA: physical activity
SPPB: Short Physical Performance Battery
WHO: World Health Organization
